
Delivery will be monitored session by session. For every session, the treating physiotherapist will complete a standardized checklist recording the exercises performed, the sets and repetitions, the progression decisions taken against the pre-specified criteria, the equipment used (Corpus VR InMotionVR/Oculus Meta Quest 3S), the session duration, and any protocol deviation together with its reason. In addition, a random sample of at least 15% of sessions in each arm will be directly observed, in person or by video recording, by an investigator not involved in delivering treatment and scored against a fidelity checklist; the proportion of key components delivered correctly will be summarized for each arm and reported. When fidelity falls below a pre-specified threshold of 80% of checklist items, corrective feedback and, where necessary, re-training will be provided. To confirm that the intervention is not only delivered but also received and enacted, participants’ understanding and correct performance of the prescribed exercises will be verified at each session, and completion of any home exercises will be captured in the eCRF. To minimize cross-contamination between arms, the experimental components—visual biofeedback, mirror, and virtual-reality equipment—will be used only during scheduled experimental-group sessions and will not be accessible to control participants; the two groups will be treated in separate rooms and, where scheduling permits, at separate times; control participants will not receive any of the experimental modalities; and participants will be asked not to seek additional physiotherapy or the experimental modalities outside the trial, with any co-interventions recorded in the eCRF and any suspected contamination documented and reported. All fidelity data, comprising the session checklists, observation scores, recorded deviations, and contamination reports, will be reviewed periodically by the principal researcher ([name]) as part of the trial’s internal monitoring, and a summary of fidelity, including the percentage of audited sessions and the mean component-delivery scores, will be reported alongside the trial results.

### 2.4. Outcome Measures

Participants will undergo five standardized assessments across the postoperative follow-up, scheduled at week 2 (baseline), week 6, week 12, week 24 (~6 months), and week 52 (12 months). The baseline assessment (week 2) will capture demographic variables and potential confounders together with the pre-intervention values of all efficacy outcomes, establishing the reference against which subsequent change is estimated. Outcomes are organized hierarchically. The single primary (confirmatory) outcome is the adjusted between-group difference in passive knee extension ROM at the 6-week postoperative assessment—the timepoint at which the intervention is hypothesized to exert its principal effect and the only outcome for which the trial is powered (Section 2.5). Passive knee extension ROM at the later assessments (24 weeks and 12 months) and all remaining efficacy outcomes—pain intensity (VAS), kinesiophobia (TSK-17), pain-related anxiety (PASS-20), knee function (KOOS), isometric quadriceps strength, and thigh circumference—are designated secondary and exploratory (hypothesis-generating). Re-tear and adverse events are safety outcomes. Two physiotherapists who are not part of the research team will perform the measurements. They will be blind to group assignments to avoid possible biases in the measurement.

#### 2.4.1. Primary Outcome Measure

Knee extension will be measured by the Baseline goniometer (precision: ±2°) for passive knee ROM. Passive knee extension ROM was selected as the primary outcome because a loss of terminal knee extension is the most prevalent early impairment after ACL reconstruction and is consistently associated with quadriceps weakness, gait asymmetry, poor knee function, an increased risk of knee osteoarthritis, and higher re-injury rates [8,9,10]. Extension will be measured in the supine position. The goniometer axis will be placed over the lateral epicondyle of the femur, the proximal arm will be placed on the lateral midline of the femur, and the distal arm will be placed on the lateral midline of the fibula. Each movement will be measured three times, and the average of these measurements will be used for the analysis. The goniometer has good intra-rater reliability (with an intraclass correlation coefficient of 0.90–0.99) when consistent body landmarks are used [32]. For ROM, the minimal clinically important difference (MCID) has not been established.

#### 2.4.2. Secondary Outcome Measures

Pain intensity will be assessed using the VAS, which consists of a horizontal line 10 cm in length, where the left end represents 0 or “painless” and the right end represents 10 or “worst pain imaginable.” The participant will be asked to mark with a vertical line the magnitude of the pain that they feel at the time of the evaluation. It is a one-dimensional, simple, and reproducible assessment method [33]. The MCID has not been established for the VAS. Fear of movement will be assessed with the original 17-item Tampa Scale of Kinesiophobia (TSK-17). Each item is scored on a 4-point Likert-type scale that ranges from strongly agree (1) to strongly disagree (4). The total score ranges from 17 to 68. A higher score indicates more fear of movement and/or (re-)injury [34]. The MCID has not been established for the TSK-17. The anxiety level associated with pain will be evaluated with the Pain Anxiety Symptoms Scale Short Form 20 (PASS-20) scale. It comprises 20 items that uses a 6-point Likert scale from 0 (never) to 5 (always). This instrument has four dimensions: cognitive anxiety, pain related fear, escape and avoidance, and physiological anxiety. The total score ranges from 0 to 100 points, with a higher score indicating a higher level of pain related to pain [35]. The MCID has not be established for the PASS-20.

Knee function will be evaluated with the Knee Injury and Osteoarthritis Outcome Score (KOOS) questionnaire. This instrument contains 42 items, including five subscales: symptoms, pain, daily life activities, sports/recreation, and quality of life. The maximum score is 100 points, which indicates greater functionality. This questionnaire has proven to have good validity and inter-rater reliability [36]. The MCID is 18.3 points [37]. Isometric muscle strength will be evaluated with the ActivForce digital dynamometer. Testing will be performed with the participant seated on a standardized testing chair, hip flexed to 90° and knee flexed to 60°, trunk upright and arms crossed over the chest. The pelvis and the distal thigh will be stabilized with inelastic straps to prevent compensatory hip and trunk movement, and the dynamometer will be positioned perpendicular to the tibia at a fixed point 5 cm proximal to the medial malleolus, recorded for each participant to ensure consistency across assessments. Three maximal “make” tests of 3–5 s (“push as hard as possible, push, push, push”) each will be performed with 30 s of rest, and the peak value will be used for analysis. This method has proven to have good validity and reliability [38]. For anthropometry, a measuring tape will be used to assess the thigh perimeter of the affected and healthy limbs before and after treatment. The circumference of the muscle will be evaluated with the tape measure located 15 cm above the upper edge of the patella. Previous studies have demonstrated the reproducibility of this method [39].

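### The printed TSK-17 response anchors and the stated score direction appear inconsistent, and no recoding rule reconciles them; if most items are fear-worded, scoring as printed flips the sign of this exploratory outcome

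*Protocol article*

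**What the plan says.** Section 2.4.2 of the protocol article measures fear of movement with the "original 17-item Tampa Scale of Kinesiophobia (TSK-17"). It makes three statements about the score:

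- on the anchors, each item "ranges from strongly agree (1) to strongly disagree (4");
- on the range, the sum over all 17 items lies between 17 and 68;
- on the direction, "A higher score indicates more fear of movement and/or (re-)injury".

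It does not reproduce the items, say how they are worded, or mention reverse-scored items or recoding.

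Section 2.4 gives the status of the outcome. Kinesiophobia is among those that "are designated secondary and exploratory (hypothesis-generating"). Passive knee extension at 6 weeks is the primary outcome and "the only outcome for which the trial is powered". Section 3 reports secondary outcomes as baseline-adjusted mean differences with 95% confidence intervals.

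**The concern.** On a scale that asks how far a person agrees with statements about fear of movement, the ordinary expectation is that agreeing signals fear. The printed anchors give agreement the lowest value, yet the total is read as rising with fear. The PASS-20 description in the same section shows the usual pattern: its anchors run from never (0) to always (5), and a higher total is worse. The TSK-17 description does not follow that pattern.

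This is more than detail left to a later document. The article states a numerical rule and a direction that do not fit together as they stand. If the form, database labels or syntax were built from the printed rule, a participant with much fear could be recorded as having little. Because the result will be read mainly from the sign of the adjusted difference, a benefit could be reported as a harm, or the reverse. A hypothesis-generating result with the wrong sign can mislead whoever designs the next trial.

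**Working it through.** **Inputs.** From Section 2.4.2: 17 items, each scored 1 to 4, with strongly agree = 1 and strongly disagree = 4; total 17 to 68; higher means more fear. Not in the documents, so treated as an assumption and ranged: k, the number of items for which agreement means fear.

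**Step 1: reproduce the stated range.** 17 × 1 = 17 and 17 × 4 = 68. The range reproduces exactly.

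**Step 2: can the range show which way the anchors run?** Swapping the anchors turns an item score s into 5 − s. Over 17 items a total T becomes 17 × 5 − T = 85 − T. The limits 17 and 68 exchange places, so the range is the same either way. The agreement in Step 1 is therefore no evidence that the anchors are right.

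**Step 3: effect of scoring as printed, with no recoding.** Let f (1 to 4) be the level of fear that an item should record. A fear-worded item scored as printed gives 5 − f; an item where disagreement means fear gives f. If the true group difference is the same on every item, d per item, the true total difference is D = 17d. The recorded difference is

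−k·d + (17 − k)·d = (17 − 2k)·d = D × (17 − 2k)/17.

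For an illustrative true difference of −4 points (less fear in the experimental arm):

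| k | Total, no fear at all | Total, maximal fear | Multiplier | True −4 is recorded as |
|---|---|---|---|---|
| 17 | 68 | 17 | −1.00 | +4.00 |
| 13 | 56 | 29 | −0.53 | +2.12 |
| 9 | 44 | 41 | −0.06 | +0.24 |
| 8 | 41 | 44 | +0.06 | −0.24 |
| 4 | 29 | 56 | +0.53 | −2.12 |
| 0 | 17 | 68 | +1.00 | −4.00 |

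The sign is wrong for every k of 9 or more. Near k = 8 or 9 the main damage is that the difference almost vanishes. At k = 0 there is no conflict.

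**Step 4: effect if items are first aligned.** If items worded the other way are recoded so that all 17 point the same way, and the printed anchors are then applied to statements of fear, the reversal is exact: T becomes 85 − T. For example, 30 becomes 55, 40 becomes 45 and 68 becomes 17.

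**Step 5: would the planned checks catch it?** Section 2.9 describes range, logic and legal-value checks in EpiData, and double entry of a 10% sample of each secondary-outcome field, reconciled to the paper form. Reversed items remain between 1 and 4, and reversed totals between 17 and 68, so range checks pass. If the paper form carries the printed anchors, both entries agree with it and with each other. In the exact-reversal case the baseline and follow-up totals are both reflected, so the adjusted group difference changes sign while partial eta squared, which carries no sign, stays the same.

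**The case against.** The strongest reply is that this is a slip in a short description. The article condenses a fuller protocol, names the original instrument, cites a source for its scoring and puts the intended direction on record. Nothing shows that the printed form or the EpiData labels use the printed anchors, and Section 2.9 gives no TSK coding. If item responses are kept, recoding each as 5 − x before analysis loses nothing. The outcome is exploratory, and Section 3 rules out confirmatory claims from it.

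Much of this stands. A misprint with a correctly scored form is quite possible, the error would be recoverable from item-level data, and the consequence is limited. What does not follow is that the line can be left alone. The direction sentence tells the analyst how to read the total, not how to build it, and the only rule given for building it points the other way on an ordinary reading. Recovery also requires that somebody notices, and the planned data checks would not prompt them.

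A reader might infer something stronger: that the scoring certainly contradicts the direction and that the kinesiophobia result will come out reversed. The documents do not support that. They give neither item wording nor keying, so both the conflict and its size depend on k. Full reversal needs all 17 items fear-worded, or items aligned before the printed anchors are applied. The documents also cannot settle which of the two sentences is wrong.

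**Conclusion.** The point holds in conditional form. The anchors and the direction appear inconsistent unless the items are worded so that disagreement means fear, and the article gives no recoding rule to reconcile them. On the assumption that most items are statements of fear, scoring as printed flips the sign of the between-group difference. With no recoding and a difference that is uniform across items, the size of the distortion runs from complete reversal when all items are fear-worded, through near-cancellation when the wording is about evenly split, to none when no item is.

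A reader might also infer a threat to the trial's main conclusion. There is none: the 6-week knee extension comparison, its sample size and its type I error do not involve the TSK-17. The correction is still worth making, because the error would be silent and fear of movement is an outcome named in the abstract.

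**What to change.** Before first data entry:

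1. Compare both sentences in Section 2.4.2 with the instrument form that will be used, and correct whichever is wrong. If the items are fear-worded, the anchors should read strongly disagree = 1 to strongly agree = 4.
2. State which items, if any, are reverse-scored, and that they are recoded before summing.
3. Check the printed form and the EpiData value labels against the corrected text, and store item-level responses so that the total can be rebuilt.

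The cost is one line in the protocol and a short check of the form and labels. The timing allows it: Section 2.6 points to referral of participants by October 2026, and the Conclusions state that no outcome data exist yet. No change to the design, sample size or analysis model is needed.

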#### 2.4.3. Potential Confounders

Comorbidities that may affect graft consolidation, meniscus tear, and outcome measures—including hypercholesterolemia, diabetes, and tobacco and alcohol consumption—will be evaluated with a data collection notebook. The dominant side, time of surgery, and treatments received prior to surgery will be recorded (physiotherapy and use of drugs, such as nonsteroidal anti-inflammatory drugs, analgesics, and opioids). Weight, height, and body mass index (BMI) will be evaluated with a SECA 213 stadiometer. BMI will be calculated as the weight (in kilograms) divided by the height (in meters) squared. The education level will be recorded as primary, secondary, technical-higher, or university. The level of physical activity will be assessed by the Global Physical Activity Questionnaire (GPAQ). This instrument was originally designed by the World Health Organization to be administered by an interviewer to assess physical activity. The questionnaire comprises 16 items that quantify the participant’s physical activity level within a normal active week to estimate the total weekly volume of moderate-to-vigorous physical activity. It includes three domains: work, transportation, and recreational activities. This questionnaire has demonstrated consistent validity and reliability [40]. For the socio-economic status, the education level will be classified as primary education (functionally illiterate, without any studies, or those who have not completed primary education), middle education (primary education, high school/secondary education, or baccalaureate), and university education (college or PhD degree). Occupation will be categorized as heavy load, light load, and sick leave in the last month.

### 2.5. Sample Size Calculation

The sample size was estimated in G*Power v3.1 (a priori, two independent means, two-sided; α = 0.05; power = 0.80). The expected effect on knee extension was informed by Liu et al. [29] in a randomized controlled trial of contralateral cross-education in early post-operative ACL reconstruction that assessed knee range of motion by goniometry and reported a significantly greater improvement in the cross-education group (group × time interaction partial η^2^ = 0.21, *p* < 0.01; a between-group difference in ROM improvement of ≈4°). Rather than power the trial on the large effect implied by that study, we adopted a conservative target: with 24 analyzable participants per group, the trial has 80% power (two-sided α = 0.05) to detect a standardized between-group difference of d ≈ 0.83 (partial η^2^ ≈ 0.15), smaller than the effect reported by Liu et al. Allowing for 20% attrition, this yields 29 participants per group (58 total). As a sensitivity analysis, under the proposed sample size, the trial detects a between-group difference of d ≈ 0.75 (29 per group) to d ≈ 0.83 (≈24 analyzable per group), corresponding to approximately 2.2–3.3° of passive knee extension for a plausible standard deviation of 3–4°—a magnitude bracketing the ≥3° extension clinical deficit associated with poorer outcomes [41]. Because the primary analysis is a repeated-measures ANCOVA adjusting for the baseline outcome value, this *t*-test-based estimate is conservative relative to the planned analysis.

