## Abstract

**Background**: Based on the available evidence, there are no published clinical trials that have analyzed the effectiveness of adding cross-education, mirror therapy, and virtual reality exercises (combined) to standard treatment to improve clinical outcomes in patients after anterior cruciate ligament (ACL) reconstruction. **Methods**: A total of 58 patients with ACL reconstruction, aged 18–50 years, will be randomized (1:1) to two treatment arms. The control group (n = 29) will receive a standard physiotherapy program based on a consensus developed by the Sport and Health Rehabilitation Guidelines. The experimental group (n = 29) will receive a novel physiotherapy program that includes cross-education exercise with visual biofeedback, mirror therapy, and virtual reality in addition to the standard exercise program. Five evaluations will be performed: at the beginning of physiotherapy treatment (baseline), at 6 weeks, 12 weeks, 24 weeks and 52 weeks after surgery. The primary outcome will be passive knee extension range of motion at 6 weeks (for sample size), assessed by goniometry; the remaining outcomes are secondary and exploratory. The secondary outcomes measures will be pain intensity, fear of movement, the level of anxiety, knee function, and isometric quadriceps strength. **Discussion**: We hypothesize that patients who receive a novel physiotherapy program that includes cross-education with visual biofeedback, mirror therapy, and virtual reality will show greater benefits in knee extension and other clinical outcomes than those who receive a standard physiotherapy program. **Conclusions**: The trial proposed in this protocol will provide new data on the effectiveness of the combination of cross-education, motor imagery, and virtual reality therapy added to a standard physiotherapy program compared with the standard physiotherapy program alone in patients who undergo ACL reconstruction. The findings will generate new insights into the effects of the interventions and expand the multimodal rehabilitation strategies available to patients who undergo this surgery.

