
The main strength of this protocol is its consideration of important methodological factors. The participants will be randomly assigned to both groups through a hidden allocation sequence. Furthermore, the sample size has been adjusted to consider the possibility of losses or dropouts, increasing the number of patients recruited by 20%, and, in the event of losses or withdrawals, a statistical analysis will be conducted by intention to treat. To minimize measurement bias, all evaluations will be performed by trained physiotherapists who are not part of the research team and will remain blinded in relation to the treatment groups. The statistician will also remain blinded to the group assignment. The outcome measures are suitable and frequently used in clinical practice, and they have a good level of validity and reliability. Finally, several further limitations should be acknowledged. First, it will not be possible to blind the participants and the physiotherapists involved in the study due to the nature of the interventions being studied. Second, self-report questionnaires will be used to assess some outcomes; they are prone to subjectivity and recollection bias. Third, the trial will be conducted at a single center, which may limit the generalizability of the findings. Eligibility is restricted to participants with a normal body mass index (18.50–24.99 kg/m^2^), so the results may not extend to overweight or obese patients. Fourth, because the experimental program combines three components (cross-education, mirror therapy, and virtual reality), the design does not allow the isolated effect of any individual component to be determined. Such an effect might reflect cross-education, mirror therapy, virtual reality, or their interaction, and could additionally be influenced by non-specific factors that co-vary with the experimental arm—greater therapist attention, the novelty of technology, higher patient engagement and motivation, and a larger effective therapeutic dose. Therefore, the trial cannot support component-specific causal inference, which is beyond its scope. Finally, the sample size was powered for the primary outcome; the trial may therefore be underpowered to detect between-group differences in the secondary and longer-term (12-month) outcomes, which should accordingly be interpreted as exploratory. In addition, the 12-month follow-up does not extend to formal return-to-sport testing; future studies should incorporate objective, criterion-based return-to-sport test batteries as recommended in contemporary consensus recommendations [56].

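### The 20% attrition allowance is applied as 24 × 1.2 rather than 24 / 0.8, so 29 per group keeps 24 analysable only up to about 17% loss; the effect on power is minor

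*Protocol article*

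**What the plan says.** Section 2.5 sizes the trial in G*Power with these settings: "a priori, two independent means, two-sided; α = 0.05; power = 0.80". The target is a "standardized between-group difference of d ≈ 0.83", and the power statement is conditional on the number analysed: "with 24 analyzable participants per group, the trial has 80% power". The attrition step follows: "Allowing for 20% attrition, this yields 29 participants per group (58 total").

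The same section gives a sensitivity range for the detectable effect, "d ≈ 0.75 (29 per group) to d ≈ 0.83 (≈24 analyzable per group"), which it converts to about 2.2–3.3 degrees for an SD of 3–4 degrees. It closes by saying that the t-test-based "estimate is conservative relative to the planned analysis", because the primary analysis adjusts for the baseline value.

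The Discussion (Section 4) counts the allowance among the protocol's strengths and says how it was made: by "increasing the number of patients recruited by 20" per cent. Allocation is equal; the Abstract says that patients "will be randomized (1:1) to two treatment arms".

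**The concern.** An attrition rate is normally read as the proportion of randomised participants who are lost. On that reading, the number to randomise is the analysable number divided by one minus the rate. The plan instead adds 20% to the analysable number. This gives a smaller figure, and the 24 analysable participants that the power statement depends on are not what remains after the loss it names.

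What is at stake is the agreement between three published figures: 24 analysable, 20% attrition and 29 randomised. Any two of them fix the third, and here they do not fit together. A reader who takes the 20% at face value will believe that the trial keeps its stated power at that rate of loss, when by the plan's own test it falls slightly short.

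**Working it through.** **Inputs.** From Section 2.5: two-sample t-test, two-sided α = 0.05, target power 0.80, d = 0.83, 24 analysable per group, 20% attrition, 29 randomised per group, SD 3–4 degrees. From the Abstract: 1:1 allocation. From the Discussion: recruitment raised by 20%.

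**Formula for power.** With n per group, the t statistic has 2n − 2 degrees of freedom and noncentrality d × √(n/2). Power is the two-sided rejection probability under the noncentral t distribution, as in G*Power.

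**Step 1: the plan's own figures.**
- n = 24, d = 0.83: noncentrality 0.83 × √12 = 2.88, power 80.4%. The d detectable with 80% power is 0.826. The smallest n reaching 80% at d = 0.83 is 24.
- n = 29: the d detectable with 80% power is 0.749.
- Range in degrees: 0.749 × 3 = 2.2 and 0.826 × 4 = 3.3.

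All of these match Section 2.5.

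**Step 2: the attrition step.**
- Adding 20%: 24 × 1.2 = 28.8, rounded up to 29. This is the plan's figure and the method that the Discussion describes.
- Allowing for 20% loss among those randomised: 24 / (1 − 0.20) = 30 per group, 60 in total.
- Difference: 1 per group, 2 in total.
- Loss that 29 per group can bear while keeping 24: (29 − 24) / 29 = 5/29 = 17.2%.
- Left after 20% loss: 29 × 0.8 = 23.2 per group, or 58 × 0.8 = 46.4 in total.

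**Step 3: power at the stated 20% loss.**

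| Analysed per group | Power at d = 0.83 | d detectable with 80% power |
|---|---|---|
| 24 and 24 | 80.4% | 0.826 |
| 23 and 24 | 79.5% | not computed |
| 23 and 23 | 78.6% | 0.845 |

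In degrees, d = 0.845 is 0.845 × 3 = 2.5 to 0.845 × 4 = 3.4. The shortfall at 23 per group is 80 − 78.6 = 1.4 percentage points.

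**Step 4: allowing for baseline adjustment.** With one baseline covariate correlated ρ with the outcome, d is divided by √(1 − ρ²) and one degree of freedom is lost. The article gives no value of ρ, so the values below are assumptions.

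| Assumed ρ | Power at 23 per group, d = 0.83 |
|---|---|
| 0 | 78.6% |
| 0.2 | 80.2% |
| 0.3 | 82.2% |
| 0.5 | 88.8% |

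**The case against.** The best defence is that the power statement is conditional and correct. Section 2.5 claims 80% for 24 analysable per group, and that reproduces. It makes no claim for 23. This stands. A reader might infer from the attrition slip that the 80% figure is false or that the trial is materially underpowered. The documents support neither, because the fault is confined to the step from 24 to 29.

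A second argument is that the planned analysis has margin the t-test ignores. Section 2.5 says so, and an assumed baseline correlation of about 0.2 is enough to bring 23 per group back to 80%. This also stands as a reason to call the effect minor. But the article states no correlation, so the margin is not quantified, and it does not make 24 the result of losing 20% of 29.

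Third, the 20% is not tied to week 6. The primary assessment comes four weeks after the week-2 baseline in a trial followed to week 52, so loss by then may be lower. That is fair: 23 per group is what remains only if the full 20% is missing at the primary endpoint. Yet the plan itself uses the 20% to protect the number analysable for that endpoint. Multiple imputation of all randomised participants does not alter the arithmetic either, since the plan sizes on analysable participants.

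Two further readings are tempting and should be set aside. The range of 2.2–3.3 degrees might look wrong because its lower end assumes no loss. But both ends are labelled with their group sizes and both reproduce, so it needs no correction. The Discussion sentence might be called false, but it describes literally how 29 was reached. It needs only to be aligned with Section 2.5.

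**Conclusion.** The attrition statement in Section 2.5 is wrong as written. Twenty per cent loss calls for 30 per group (60 in total) if 24 are to remain, and 29 per group covers about 17%. If the full 20% is lost by week 6, about 23 per group remain and unadjusted t-test power at d = 0.83 is about 79%. By that test, 80% power then holds at d = 0.845, about 2.5–3.4 degrees for the plan's SD of 3–4 degrees.

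The discrepancy is two patients and 1.4 percentage points, and a modest baseline correlation, which would have to be assumed, would close it. This is a small error in a published figure that should be corrected, not evidence of a material loss of power. The result rests on reading attrition as a proportion of those randomised and on equal losses in the two groups.

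**What to change.** Keep 58 and restate the allowance in Section 2.5, for example:

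> Randomising 29 per group (58 in total) allows for about 17% attrition while retaining 24 analysable participants per group. At 20% attrition (about 23 per group), the unadjusted t-test has about 79% power for d = 0.83, or 80% power for d = 0.845 (about 2.5–3.4° for an SD of 3–4°).

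Keep the existing remark that the baseline-adjusted ANCOVA is expected to be more efficient than the t-test. Describe the allowance in the Discussion in the same terms. Leave the 2.2–3.3 degree range as it is.

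The cost is wording and a slightly less favourable stated figure; no extra patients are needed. If the investigators prefer to keep the 20% label, the consistent number is 60 randomised, two more than planned.
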